### Intervention arms and study procedures

#### Study arms.

Intervention Arm: Participants randomized to the Early Intervention Arm will receive access to MyIBDDiet App (Fig 3A and 3B) for 60 days. Participants will have access to all the features of the app including diet and symptom tracking, information on level of food processing, adherence to mediterranean-style eating, ability to correlate diet with bowel symptom severity and access to nutrition education resources. Use of the app is self-directed and participants will be encouraged to engage with the features as needed to support self-management. They are not required to use the app on a daily basis or for a set period of time. App engagement metrics will be collected at the backend to assess utilization patterns.

**Fig 3 pone.0353123.g003:**
[figure not shown]
Snapshots of MyIBDDiet App illustrating various features of the app. (A) MyIBDDiet App is a nutrition education app co-developed by academic researchers and patient research partners. This figure shows snapshots of app features, explained as follows: (i) MyIBDDiet App landing and login screen (ii) MyIBDDiet App dashboard shows the food log, visual analogue scale for tracking bowel symptoms and taking notes (iii) shows food log with number tagging for level of processing where four indicates ultra-processed and one indicates no/minimal processing (iv) shows the nutritional information including caloric intake, protein intake, fibre and sodium intake amongst other parameters. Reprinted from https://myibddiet.vercel.app/ under a CC BY license, with permission from Seca Innovations, original copyright [2026] Fig 3B: Snapshots of MyIBDDiet App illustrating various features of the app. (B) This figure shows snapshots of app features, explained as follows: (i) shows the reports section- where the calendar shows the severity of bowel symptoms on each day of the month (ii) shows the breakdown of food items according to the level of processing and alignment with Mediterranean style eating. This feature can be adjusted to see a long-term trend over a week or a month (iii) shows the resources and nutrition educational videos created on topics like ultra-processed foods, recognition and replacement and information on anti-inflammatory diets such as Mediterranean diet (iv) shows the use of the barcode scanner to identify additives and emulsifiers in foods. Reprinted from https://myibddiet.vercel.app/ under a CC BY license, with permission from Seca Innovations, original copyright [2026].

Control Crossover Arm: Participants will continue on the usual care for the first half of the study (first 30 days). Usual care represents any dietary advice or recommendations that the treating gastroenterologist may or may not provide the patient as part of usual care or what patients may be using on their own. Currently there are no standardized resources at our center but patients can be referred to an IBD dietitian. Providers typically direct patients to the Crohn’s Colitis Canada website. For the latter half of the study, participants will crossover to the MyIBDDiet App.

### Study procedures

The research coordinator will conduct the study at the clinic in person. Study procedures are outlined below:

Participant characteristics: Baseline characteristics, such as demographics, details of IBD diagnosis, therapies and disease activity, will be obtained from the participant and by reviewing their medical charts at the baseline visit (Day 0).

Anthropometrics: Anthropometric measurements, including height, weight, waist circumference and waist-to-hip ratio will be recorded at each clinical visit (Baseline, Day 30 and Day 60).

Nutritionally relevant questionnaires: Participants will be asked to complete a series of nutritionally relevant questionnaires, including the ASA24^®^ Dietary Assessment Tool and the Mini-EAT™ diet quality questionnaire. These will be completed at baseline, day 30, day 60 and day 180.

ASA24^®^: The ASA24^®^ is an electronic, self-automated, 24-hour dietary recall tool developed to assess dietary intake data. Using the Canadian version of the ASA24^®^ (ASA24-Canada-2018), each participant will log all self-reported food and beverage intake from a 24-hour period for two previous weekdays and one previous weekend day [43]. They will also have the option to complete ASA24 in an interviewer-led way where a member of the study team will collect the dietary recall data from the participant and log in ASA 24 on their behalf. The Healthy Eating Index Score (HEI) [44] and Mediterranean Diet Serving Score (MDSS) [45] will be calculated based on the food recall data obtained from ASA24.Mini-EAT™: 9-item Mini-EAT™ is a short diet quality screener which has been validated for use in clinical settings [46]. It is scored based on the frequency of consumption of fruits, vegetables, grains (whole and refined), legumes, seafood, dairy (low and high fat), sweets and sugary drinks [46].

Quality of Life questionnaires: Health related quality of life will be assessed by EQ-5D and SIBDQ questionnaires.

EuroQoL-5 Dimensions (EQ-5D): EQ-5D assesses health related quality of life across five dimensions: mobility, self-care, usual activities, pain or discomfort and anxiety or depression [47]. Each dimension has five levels of severity [47]. The questionnaire also uses a visual analogue scale that allows participants to quantitatively describe their overall health on the day of completing the questionnaire [47].Short Inflammatory Bowel Disease Questionnaire (SIBDQ): SIBDQ is an IBD-specific, widely used and validated quality of life tool that features 10 questions across four domains: Bowel symptoms, Systemic symptoms, Emotional function and social function [48].

Usability and Acceptability questionnaires:

mHealth App Usability Questionnaire (MAUQ): MAUQ is a validated tool used to assess the usability of mobile health applications from the user’s perspective. It evaluates usability across key domains, including overall participant satisfaction, system information arrangement and usefulness [49]. Domain-specific and overall scores will be calculated.Theoretical Framework of Acceptability (TFA): The acceptability of the intervention was assessed using the TFA questionnaire, structured to measure acceptability across the key constructs of affective attitude, burden, ethicality, intervention coherence, opportunity costs, perceived effectiveness and self-efficacy [50].

Semi-structured Interviews: Semi-structured interviews will be conducted virtually via an online conferencing platform. All the participants who initiated the intervention will be invited to participate in the interviews. The interview questions have been framed using the CFIR framework [51] and the focus of the interview is to identify barriers and facilitators to the use of MyIBDDiet App (S2 File). Interviews will be conducted by research team members experienced in conducting qualitative research. All identifying information will be removed and interviews will be transcribed verbatim.

Biological specimen collection and analytical procedures: C-reactive protein and fecal calprotectin levels will be collected for assessing disease activity as per standard of care. Urine sodium and chloride levels will be measured using a dipstick test to relate to processed foods consumption. Spot urine sodium has been used in studies to help validate processed food questionnaires [52]. We have also elected to use spot urine chloride as the availability of urine sodium strips are limited and urine chloride strips have been validated against 24-hour urine excretion and found to provide reasonable approximation [53]. Stool samples will be collected and processed for 16S rRNA sequencing to assess microbial composition. As the accuracy of diet questionnaires can be challenging in clinical trials, we will be collecting stool and serum samples to evaluate metabolite signatures to correlate with the diet questionnaire data [54]. We will perform untargeted metabolomic profiling using chemical isotope labelling liquid chromatography-mass spectrometry (CIL LC-MS).

### Primary, secondary and exploratory outcomes

The primary outcome of usability will be evaluated using a mixed-method quantitative [mHealth App Usability Questionnaire (MAUQ) and Theoretical Framework of Acceptability (TFA)] and qualitative (semi-structured interviews) approach.

Secondary outcomes of interest include clinical efficacy evaluated by change in diet quality [Mini-EAT questionnaire, Automated Self-administered 24-Hour Dietary Assessment Tool (ASA-24), Healthy Eating Index (HEI), Mediterranean Diet Serving Score (MDSS)], urine sodium and chloride (biomarkers of processed food intake), changes in disease activity [Patient Reported Outcome (PRO2 UC and PRO3 CD), C-reactive protein, fecal calprotectin] and changes in quality of life [EQ-5D, SIBDQ]. Behaviour changes and diet knowledge will be assessed objectively by measuring changes in diet quality scores, changes in the nutrient intake data obtained from ASA 24 and subjectively by assessing responses to individual questions on changes in diet in the semi-structured interview. To assess safety, systematic monitoring of adverse events and serious adverse events will be done at each time point and in between time points if symptoms worsen.

Exploratory outcomes include changes in fecal microbiome and serum and fecal metabolites to correlate with change in diet and disease activity.

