## Objectives

This pilot study is designed to explore a structured approach to the evaluation of a mobile health app to empower self-management for people living with IBD. The primary study objectives are to evaluate the usability and acceptability of the MyIBDDiet app. The secondary objectives include evaluating the efficacy of the app in improving diet quality, diet knowledge, disease control, safety and quality of life.

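### Diet knowledge is a separate efficacy objective, but its only quantitative measures are self-reported eating scores, so the trial cannot estimate an app effect on knowledge

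*Protocol article*

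**What the plan says.** The Objectives section states: "The secondary objectives include evaluating the efficacy of the app in improving diet quality, diet knowledge, disease control, safety and quality of life". Diet quality and diet knowledge are two separate entries in that list.

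The section on primary, secondary and exploratory outcomes says how knowledge is to be assessed. It shares one sentence, and one set of measures, with behaviour change:

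- the first measure is given as follows: "Behaviour changes and diet knowledge will be assessed objectively by measuring changes in diet quality scores";
- the second is how nutrient figures from the ASA24 recalls move over time;
- the third is the interview, where knowledge is assessed "subjectively by assessing responses to individual questions on changes in diet in the semi-structured interview".

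The first two are labelled objective and the third subjective.

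Study procedures describes the instruments behind these measures. For ASA24, "each participant will log all self-reported food and beverage intake from a 24-hour period". The Healthy Eating Index and the Mediterranean Diet Serving Score "will be calculated based on the food recall data obtained from ASA24". Of Mini-EAT it says: "It is scored based on the frequency of consumption of fruits, vegetables, grains", with further food groups following. The same section invites to interview everyone who began using the app, and gives the interview's focus as barriers and facilitators to app use.

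**The concern.** Knowledge and eating are different constructs. A participant can learn which foods are ultra-processed and go on eating them. A participant can also eat differently by following the app's food tags, feedback messages and barcode scanner without retaining anything. A change in a diet score therefore does not show a change in knowledge, and an unchanged score does not show that nothing was learned.

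If the plan is followed as written, one between-arm difference in diet scores would answer two objectives: once as better diet and once as better knowledge. The second answer would rest on no measurement of knowledge. Education is a core function of the app, and the pilot is meant to inform a larger efficacy trial, so an undefined knowledge endpoint could be carried forward.

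The label is a lesser matter. Calling these measures objective sits badly with the article's own description of ASA24 as self-report. The trial is open-label, and one arm is being taught during the comparison period which foods count as good choices. Reported intake could shift with allocation for that reason alone.

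**Working it through.** No arithmetic applies: the article gives no figure for knowledge and no power calculation to reproduce. The check compares the objective with each measure assigned to it, and then looks for a knowledge measure anywhere else in the article.

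**Step 1. Measures assigned to knowledge.**

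| Measure | What the article says it records | Also used for diet quality? |
|---|---|---|
| Mini-EAT | How often food groups are consumed | Yes |
| ASA24 nutrient intake | Self-reported 24-hour food and drink | Yes |
| Healthy Eating Index, Mediterranean Diet Serving Score | Calculated from the ASA24 recalls | Yes |
| Interview questions | Described as being on changes in diet | Not listed there |

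Every quantitative measure assigned to knowledge is a report of eating, and every one is already listed under diet quality. Only the interview component differs between the two objectives.

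**Step 2. Search for a knowledge measure elsewhere.** The remaining items in Study procedures, the outcomes section and the Fig 1 legend are:

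- PRO-2 and PRO-3, C-reactive protein and fecal calprotectin (disease activity);
- EQ-5D and SIBDQ (quality of life);
- MAUQ and TFA (usability and acceptability of the app);
- anthropometrics;
- urine sodium and chloride;
- microbiome and metabolites.

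None is described as testing diet knowledge. The TFA constructs concern the intervention itself. App engagement metrics, described under Study arms, record use, and a control participant has no app to use before Day 30. The number of instruments described as giving a knowledge score is therefore zero, at every visit.

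**Step 3. What the interviews can supply.** Invitation depends on having started the app. A control participant qualifies only after crossing over at Day 30, so there is no interview under usual care to compare with. No baseline interview is described. The interview date is not given, the Fig 1 schedule is not shown, and the guide (S2 File) is not shown. Items on learning cannot be ruled out, but they would give qualitative information without a randomised comparison.

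**Step 4. Where an effect could be estimated.** Controls receive the app for the second 30 days, so baseline to Day 30 is the only randomised comparison of app with usual care. An effect on knowledge needs a score at Day 30 in both arms, ideally with a baseline. The plan has neither.

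**Step 5. The label.** The outcomes section calls diet scores and ASA24 intake objective. Study procedures calls ASA24 intake self-reported, and its specimen paragraph concedes that the accuracy of diet questionnaires is a difficulty, giving that as the reason for collecting metabolite data. The measures of intake that do not depend on self-report are the urine markers and metabolites. They too concern eating, and they are not assigned to knowledge.

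**The case against.** Four arguments can be made for the plan.

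*The article is a condensed protocol.* A knowledge instrument could sit in the full document. This does not succeed: the article does not leave the method open. It states how knowledge will be assessed, and the stated method does not fit.

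*The interviews may cover knowledge.* This stands in part. With the guide and the interview timing not shown, a reader should not infer that the trial will learn nothing about knowledge, or that every interview follows completed app use. The documents support only the narrower statement that no app effect on knowledge can be estimated. Nor is it a fault of qualitative interviews as such that they lack a control group.

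*The word objectively is only a contrast.* It is paired with *subjectively* in the same sentence and can be read as separating scored instruments from participants' own accounts. The article is open elsewhere that ASA24 is self-report and that questionnaire accuracy is limited, and it already plans urine and metabolite markers of intake. A reader might infer that the sponsor means to pass off self-report as hard evidence, or has no objective marker of intake. The text supports neither. What stands is a wording conflict between two sections.

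*The stakes are small.* This is a 40-person pilot whose primary objectives are usability and acceptability, and knowledge is one of several secondary targets. That is fair and limits the severity. It does not remove the mismatch.

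**Conclusion.** The point holds in a limited form. Diet knowledge is one of five secondary targets, and it is the only one with no quantitative measure of its own. Its scored measures are self-reports of eating that coincide with those for diet quality. The interviews can add qualitative information but no comparison with usual care. The trial can therefore report whether reported diet differed between arms at Day 30, but it cannot estimate whether the app changed knowledge.

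The primary outcome, diet quality, disease activity, quality of life, safety and the variance estimates for a later trial are all unaffected. The issue deserves correction because the correction is cheap and because a baseline knowledge measure, once missed, cannot be recovered.

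The conclusion rests on the article's instrument descriptions being complete as to what each instrument measures. If the full protocol contains a scored knowledge instrument given to both arms by Day 30, the point reduces to correcting the outcomes section so that it names that instrument.

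**What to change.** Choose one of two routes.

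1. **Drop the claim.** Remove diet knowledge from the efficacy objectives and from the sentence in the outcomes section. Report the diet scores as self-reported behaviour only. Anything the interviews say about learning can be reported as qualitative findings. The cost is wording.

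2. **Measure it.** Add a short scored diet-knowledge measure at baseline and Day 30 in both arms, and analyse it as the Day-30 between-arm difference, reported with its confidence interval like the other outcomes. An existing validated instrument is preferable. A quiz written for this trial would be unvalidated, and if its items mirrored the app's tags and videos it would favour the app arm by construction. The cost is a few minutes at two visits already scheduled, plus an ethics amendment. The time is my assumption; the article gives no figure.

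Under either route, replace *objectively* in the outcomes section with *quantitatively, by self-report*, and say there that the urine and metabolite markers already planned are the objective evidence on intake. This adds no data collection.

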### Data management

We will use REDCap hosted at the University of Alberta as a secure, web-based application for data collection and management in our study. The questionnaires for participants will be completed during the clinical visit with the assistance of the research team and then transferred into the REDCap system. All study personnel will undergo Good Clinical Practice (GCP) training and be informed of their responsibilities regarding participant privacy and confidentiality through detailed protocol discussions prior to participant recruitment. Only study personnel authorized by the principal investigator will have access to study materials and data.

### Ethical approval, trial status and timeline

This study will be conducted in accordance with Good Clinical Practice guidelines and has been approved by the University of Alberta Health Research Ethics Board (HREB Biomedical – Ethics ID: Pro00141681). Recruitment is anticipated to begin in March 2026 and to complete by March 2028. Data analysis is expected to be complete by August 2028. Manuscript writing and publication of results is expected by December 2028.

### Statistical analysis plan

The main analytical steps in this study include descriptive statistics, pre-post comparisons, and between-group comparison tests. All quantitative analyses will be conducted on an intention-to-treat (ITT) basis, including all participants who undergo randomization [55]. This pilot randomized study will be conducted over 60 days, comprising two 30-day periods of app use.

Primary and secondary quantitative outcomes: To account for the repeated measures (Baseline, Day 30, Day 60, Day 180) and the crossover study design, we will utilize Linear Mixed Models (LMM) [56,57]. This approach is preferred as it handles missing data robustly via Restricted Maximum Likelihood (REML) estimation and accounts for within- subject and between-subject variability. The model will include “Group”, “Time” and “Group X Time” interactions as fixed effects, with a random intercept for each participant. In the event of model non-convergence, the random effects structure will be simplified.

Handling of missing data: We anticipate an attrition rate of 10–15%. Linear Mixed Models allow for the inclusion of participants with missing timepoints under missing at random assumption. If missing data exceeds 20%, Multiple imputations by chained Equations (MICE) will be performed [58].

Effect size and Variance: As this is a pilot study, the focus of analysis is not solely on p-values, but on point estimates and confidence intervals. We will calculate Cohen’s d effect sizes for change in quantitative outcomes to provide the necessary variance and magnitude of effect estimates required for a power calculation in a future larger trial. We will be using SPSS version 29.0.2.0 (20) for statistical analyses.

Semi-structured interviews: The interviews will be transcribed verbatim. Thematic analysis will be done independently by two researchers using Nvivo which is a qualitative data analysis software and any conflicts will be resolved by a third reviewer who is a senior gastroenterologist and principal investigator [59].

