### Trial design and setting

This protocol was developed in accordance with the SPIRIT 2013 statement (S1 File). Fig 1 shows the SPIRIT schedule of enrollment, interventions and assessments. This single-centre, open-label pilot randomized trial will be conducted at the University of Alberta hospital, a tertiary care hospital located in Edmonton, Alberta. Participants will be randomized in a 1:1 ratio to either the Intervention Arm (receiving MyIBDDiet app for the entire duration of the study, i.e., 60 days) or the Control Crossover Arm (receiving usual care as per treating physician for the first 30 days followed by MyIBDDiet App for the latter half of the study) (Fig 2). Outcomes of interest will be assessed at baseline, 1 month, 2 months, and at 6 months follow-up. The 6-month timepoint will allow for assessment of persistence of behavioral and diet quality changes.

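### The four-visit Group × Time model prescribed for the primary outcomes does not fit app ratings, which cannot exist before participants have the app

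*Protocol article*

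**What the plan says.** All references are to the protocol article.

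- **Outcomes.** The section on primary, secondary and exploratory outcomes states the following: "The primary outcome of usability will be evaluated using a mixed-method quantitative [mHealth App Usability Questionnaire (MAUQ) and Theoretical Framework of Acceptability (TFA" scales, together with interviews. Under Study procedures, "MAUQ is a validated tool used to assess the usability of mobile health applications from the user’s perspective". The TFA is described there as covering acceptability of the intervention, with constructs such as burden and perceived effectiveness.
- **Model.** Statistical analysis plan: "Primary and secondary quantitative outcomes: To account for the repeated measures (Baseline, Day 30, Day 60, Day 180) and the crossover study design" are to be handled by a linear mixed model with Group, Time and Group × Time "interactions as fixed effects, with a random intercept for each participant". No outcome is excepted. If the model does not converge, the random-effects structure is simplified.
- **Effect size.** The same section plans Cohen's d for change in the quantitative outcomes.
- **Access to the app.** Trial design and setting describes the control crossover arm as "receiving usual care as per treating physician for the first 30 days followed by MyIBDDiet App for the latter half of the study". The intervention arm has the app for all 60 days.
- **Missing data.** Attrition of 10–15% is expected, analysis is by intention to treat on everyone randomised, and "If missing data exceeds 20%, Multiple imputations by chained Equations (MICE) will be performed". The text does not say whether a rating that could not yet be given counts as missing.

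**The concern.** A usability or acceptability score, as these instruments are described, presupposes that the respondent has used the app. The model presupposes a score in each arm at each of four visits. For the MAUQ and TFA these two do not meet. The comparisons a Group × Time model is normally fitted for, change from baseline by arm and the randomised app-versus-no-app contrast at Day 30, do not exist for these outcomes. The arm comparisons that survive ask whether longer access changes the rating. The primary objective asks how usable and acceptable the app is, which calls for a level among people who have had access, with its uncertainty. As worded, the section attaches a different analysis to the trial's primary quantitative question.

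**Working it through.** **Inputs.** 40 participants, 20 per arm (Sample size); 2 × 20 = 40 agrees, and no power, alpha or SD is stated. Four visits. Attrition a = 10–15%. Imputation trigger 20%. Assumption: a MAUQ or TFA score requires app access.

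**1. Which cells can hold a rating**

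| Arm | Baseline | Day 30 | Day 60 | Day 180 |
|---|---|---|---|---|
| Intervention (early) | none | yes | yes | yes, if collected |
| Control crossover | none | none | yes | yes, if collected |

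Empty cells: 3/8 = 37.5%, or 3 × 20 = 60 of 160 scores.

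**2. Estimability.** Group + Time + Group × Time has 2 × 4 = 8 fixed-effect parameters, one per cell mean, so the rank equals the number of filled cells.

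- Ratings at every visit after access: rank 5 of 8.
- The same without Day 180: rank 3 of 8.
- Day 60 only: rank 2 of 8.

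Each contrast was tested against the row space of the design matrix for the rank-5 case, the most favourable one.

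- Not estimable: every contrast with baseline; the between-arm difference at Day 30; the Day 30–60 interaction.
- Estimable: each filled cell's mean; the between-arm differences at Day 60 and Day 180; the Day 60–180 interaction; the early arm's Day 30–60 change.

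A REML fit of the four-visit model to simulated data (n = 40) stopped with a singular matrix. The same model on Days 60 and 180 alone was fitted without difficulty. Simplifying the random effects would not help, because the deficiency is in the fixed effects. Cohen's d for change from baseline has no starting value.

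**3. The 20% rule.** Share missing = 1 − (filled cells / cells counted) × (1 − a), with five filled cells:

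| Counting rule | a = 0 | a = 10% | a = 15% |
|---|---|---|---|
| Four visits, 1 − (5/8)(1 − a) | 37.5% | 43.8% | 46.9% |
| Three post-baseline visits, 1 − (5/6)(1 − a) | 16.7% | 25.0% | 29.2% |
| Post-access visits only, 1 − (1 − a) | 0% | 10% | 15% |

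Whether the trigger is met depends on the counting rule, which the text does not give. If it is met, the cell open to imputation is control Day 30 (20 of the 40 Day 30 scores). The baseline column is wholly empty and has nothing to be imputed from.

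**4. Precision of a direct estimate.** The 95% CI half-width of a mean, in SD units, is t(0.975, n − 1)/√n.

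- Arms pooled: n = 40 × 0.90 = 36 gives 0.338; n = 40 × 0.85 = 34 gives 0.349.
- One arm: n = 18 gives 0.497; n = 17 gives 0.514.

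For a Day 60 between-arm difference the half-width is t(0.975, 2n − 2) × √(2/n): 0.677 with 18 per arm and 0.699 with 17. That contrast is about twice as imprecise as the pooled mean and compares 60 with 30 days of access.

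**The case against.** **A reader might infer that the primary analysis cannot be estimated at all.** The documents do not support that. Every cell that can hold data has an estimable mean, including early-arm Day 30 and control Day 60. Descriptive statistics come first among the listed analytical steps, the section puts weight on estimates with intervals, and Study procedures promises domain and overall MAUQ scores. The interviews, the other half of the primary outcome, are unaffected. Software that drops redundant terms would still return output, although not the contrasts the model implies. This objection stands, and it limits the point to the model as specified.

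**A reader might also infer that the plan will impute scores for people who never saw the app.** That goes too far on two counts. The missing-data paragraph begins from attrition, so it can fairly be read as covering only ratings that were due; on that reading 10–15% does not reach 20%. And controls at Day 30 have not yet received the app, which is different from never seeing it.

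**The schedule is not visible.** The text gives no visits for MAUQ and TFA; Fig 1 may, but it was not available. A form of the TFA completed before use is conceivable, though none is described. If Fig 1 restricts both scales to post-access visits, the empty cells remain, and the section still assigns a four-visit model to outcomes not measured at four visits.

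**An article condenses.** Per-outcome detail may sit in a fuller document. But the point here is a statement, not an omission: the sentence names the primary outcomes and gives them this model.

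**Conclusion.** The concern holds in this form: the prescribed model and the change effect size do not suit the primary quantitative outcomes. At least 3 of 8 cells (37.5%) are structurally empty, rank is at most 5 of 8, and the baseline and Day 30 between-arm contrasts do not exist. The arm differences left over measure length of access, not usability. Means after access can be estimated, and should be the stated primary estimate. The imputation consequence is conditional on pre-access visits being counted as missing.

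This rests on two assumptions: that MAUQ and TFA, as described, need app access, and that nobody has the app before it is allocated. The unseen schedule can only leave the number of empty cells at three or raise it. The finding does not touch the secondary outcomes, which can be measured at all four visits.

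**What to change.** 1. Remove MAUQ and TFA from the Group × Time model and from the Cohen's d for change.
2. State that visits before app access are outside the missing-data rule for these two scales.
3. Define the primary quantitative estimate as the mean with 95% CI, overall and by domain, after app access and pooled over arms. If the early arm is rated at Day 30, take it at the end of each participant's first 30 days of access (Day 30 early, Day 60 control). Otherwise take it at Day 60 in both arms and note the unequal exposure.
4. Report the early arm's 60-day score separately as longer exposure. Beside it give the number who never opened the app, which the planned back-end engagement metrics should supply.

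The cost is analysis wording only, with no added participants, provided the ratings are already scheduled at those visits. With analysis due to finish in August 2028, the change can be made before any data are analysed.
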